### Sample size calculation

According to a previous randomized controlled trial that investigated the effect of combined ketamine and pregabalin on persistent postoperative pain, the prevalence of moderate-to-severe acute postoperative pain at 24 h after surgery was 42% in the combined group and 78% in the control group [16]. Among patients with preoperative pain, the incidence of acute moderate-to-severe postsurgical pain in the population undergoing spinal surgery is nearly 80% [1]. Based on the above data and the current clinical situation, we estimate that the incidence of acute moderate-to-severe postsurgical pain will be 30% in the combined group and 60% in the control group, with a total 2-sided type I error rate of 0.05 and a 20% withdrawal rate. Ninety patients will have to be enrolled to achieve a statistical power of 80% (*P* values of 0.05).

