### Study setting and recruitment procedure

The recruitment of this trial will be conducted in Beijing Tiantan Hospital from 1 December 2021 to 31 August 2022, and the follow-up will be until 31 December 2022. Based on the electronic medical records of the hospital, potential participants will be individually screened after admission. Almost 100 patients underwent surgery in the spinal neurosurgery department at Beijing Tiantan Hospital in 1 month, and the proportion of patients with spinal neoplasms was nearly 60% in this population. The sample size is only 90 for our study. Therefore, the predicted 8-month duration of this study is enough to complete the recruitment. No extra measures will be taken to recruit a sufficient number. Participants meeting the eligibility criteria will be visited by the research staff to sign informed consent forms and provide baseline information. The flow chart of the study is shown in Fig. 1.

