### Randomization and blinding

Patients will be randomized 1 day before surgery using blocked, stratified randomization by independent research staff to 1 of 2 treatment groups (the combined group or the control group) after study enrollment. We will randomize the patients in a 1:1 ratio in blocks of four. The randomized allocation list will be generated by using a real-time, online system on the day before surgery. The randomization results will be maintained by independent researchers who will not participate in any other work of this study to guarantee allocation blinding. The presence of moderate or severe preoperative pain will be used as a basis for the stratification of patients (evaluated by a visual analog scale, range: 0–100, with 0, no pain; 100, the worst pain; moderate or severe preoperative pain is defined by a VAS score equal to or more than 40 mm).

Allocation concealment will be achieved using study capsules and intravenous infusions with identical appearance for placebo and drugs. All the trial drugs will be provided by a medicine company (Hengrui Induction, Jiangsu, China) with no other contribution to this trial. The appearance of all trial capsules (placebo capsules containing starch and pregabalin capsules) will be the same. Esketamine will be diluted to a concentration of 0.5 mg/ml with normal saline. Colorless 50-ml syringes containing clear esketamine or placebo (normal saline) solution will be prepared in a blinded manner by an independent research assistant. The randomization code will be marked on the syringes and the drug bottles of the study capsules. Only the study investigator who assigns participants to interventions will be unblinded to the treatment assignment. All other study researchers will be blinded to the treatment assignment, including responsible anesthesiologists and the neurosurgeons in charge of the patients, the outcome assessors, data analysts, and other relevant investigators.

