### Statistical analysis

Continuous data will be described as the mean with standard deviation (SD) or median with interquartile range (IQR) based on its distribution. The histogram and Kolmogorov–Smirnov tests will be used to evaluate the normality of the data distribution. Categorical variables will be summarized as counts and percentages. The primary outcome is categorical and will be analyzed by using the chi-square test or Fisher’s exact test. Regarding the secondary outcomes, based on the type of each variable, the difference between groups will be analyzed using *t* tests, Mann–Whitney *U* tests, and chi-square or Fisher’s exact tests as appropriate. We will use the modified intension-to-treat (mITT) analysis to report our results, and we will use per-protocol (PP) analysis to perform the sensitivity analysis. The methods for estimating effects and 95% CIs will be reported in our outcomes. Sensitivity analyses will be applied to determine the statistical nature of the missing data. A two-sided *P* value of 0.05 was considered statistically significant for the primary outcome. Because of the repeated measurement, the Holm–Bonferroni method will be used to adjust the *P* value for secondary outcomes. Statistical analysis will be implemented using SPSS version 23.0 software and Stata version 14.0.

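### Ninety enrolled with the plan's own 20% withdrawal gives about 73% power by the chi-square test (64% by Fisher's exact test), not the stated 80%

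*Protocol article*

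**What the plan says.** The Sample size calculation section of the protocol article gives all the inputs together. The expected incidence of acute moderate-to-severe pain is "30% in the combined group and 60% in the control group". The error rate and the allowance for loss come next: "with a total 2-sided type I error rate of 0.05 and a 20% withdrawal rate". It then states the result: "Ninety patients will have to be enrolled to achieve a statistical power of 80" per cent. No formula or software is named.

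The figure is repeated as settled under Study setting and recruitment procedure: "The sample size is only 90 for our study". Randomization and blinding fixes equal allocation: "We will randomize the patients in a 1:1 ratio in blocks of four". The Statistical analysis section leaves the primary test open between two options: "The primary outcome is categorical and will be analyzed by using the chi-square test or Fisher’s exact test".

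**The concern.** A 20% withdrawal rate listed among the inputs should raise the enrolled number above the evaluable number. For 60% against 30% the evaluable number is already in the low eighties, so a total of 90 leaves room for a loss of only several per cent. Either the 20% was not applied, or it was applied to something smaller than the stated inputs require.

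The power for the primary outcome governs how a null result is read. If readers believe the trial had 80% power when it had nearer 73%, a non-significant result will look like stronger evidence against the combination than it is. No interim analysis is planned, so no scheduled step would bring the shortfall to light.

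**Working it through.** **Inputs**
- Event rates p1 = 0.30 and p2 = 0.60, difference 0.30, mean 0.45 (Sample size calculation)
- Two-sided alpha 0.05 (z = 1.960); power 80% (z = 0.8416) (same section)
- Withdrawal 20% (same section)
- Allocation 1:1 (Randomization and blinding)
- Test: chi-square or Fisher's exact (Statistical analysis)

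**Trying to reproduce 90**

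Pooled two-proportion formula, per arm:

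n = [1.960·√(2·0.45·0.55) + 0.8416·√(0.30·0.70 + 0.60·0.40)]² / 0.30² = (1.3790 + 0.5646)² / 0.09 = 41.97, so 42 per arm and 84 evaluable. Enrolled: 84/0.8 = 105.

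Unpooled formula, per arm:

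n = (1.960 + 0.8416)²·(0.21 + 0.24)/0.09 = 39.24, so 40 per arm and 80 evaluable. Enrolled: 80/0.8 = 100.

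| Two-sided method | Per arm | Evaluable | Enrolled, N/0.8 |
|---|---|---|---|
| Unpooled | 40 | 80 | 100 |
| Pooled | 42 | 84 | 105 |
| Arcsine | 42 | 84 | 105 |
| Mean-rate variance throughout | 44 | 88 | 110 |
| Log odds ratio (Wald) | 45 | 90 | 113 |
| Continuity-corrected (close to Fisher) | 49 | 98 | 123 |

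Multiplying by 1.2 instead of dividing by 0.8, a common slip, gives 96 (unpooled) or 101 (pooled). Two routes come near 90. The log-odds-ratio formula gives exactly 90, but before any withdrawal. A one-sided calculation with mean-rate variance gives 35 per arm and 35/0.8 = 44 per arm, 88 in all, but the plan states a two-sided error. None of the two-sided methods tried gives 90 after 20% withdrawal.

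**Power that 90 enrolled delivers**

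90 × 0.8 = 72 evaluable, 36 per arm. Pooled approximation: (0.30·√36 − 1.3790)/√0.45 = (1.8 − 1.3790)/0.6708 = 0.628, and Φ(0.628) = 73.5%. The exact figures below sum the binomial probabilities of every pair of outcomes that the test declares significant.

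| Method | 36 per arm (20% lost) | 45 per arm (none lost) |
|---|---|---|
| Pooled approximation | 73.5% | 82.8% |
| Unpooled approximation | 76.5% | 85.1% |
| Exact, uncorrected chi-square | 72.7% | 81.8% |
| Exact, Fisher | 63.6% | 75.8% |

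**Loss that 90 enrolled can absorb at 80% power**
- Pooled formula: 84 of 90 evaluable, loss of 6.7%
- Exact chi-square: 82 of 90, loss of 8.9% (power 81.3% at 41 per arm, 79.6% at 40)
- Unpooled formula: 80 of 90, loss of 11.1% (power 80.7% at 40 per arm)
- Fisher: not reached even with no loss

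**The case against.** The strongest reply is that the 20% need not apply to the primary outcome. That outcome covers the first 48 hours and is collected by bedside interview in hospital, whereas later outcomes run to 3 months and are collected by telephone. The main analysis is modified intention-to-treat, so a patient who stops study drug but still reports a pain score need not be lost. With no loss, exact chi-square power is 81.8%. This stands as a reason to expect a smaller shortfall in practice. It does not rescue the statement, because the plan makes 20% an input to this very calculation. If the 20% does not apply, the assumption is misstated; if it does, the power is.

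A second reply is that Fisher's test would hardly be used. At 36 per arm and a mean rate of 45% the smallest expected cell is 36 × 0.45 = 16.2, far above the counts that usually prompt it. That is fair: about 73% is the main figure, and 64% is a lower value that matters only because the plan leaves the choice open.

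A third is that the tolerable loss depends on the formula. That is also right, so any figure quoted for it must name its method. Finally, the shortfall affects neither the type I error nor the effect estimate, and the plan promises 95% confidence intervals, which would temper the reading of a null result.

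**Conclusion.** The concern holds. The stated inputs call for 80 to 84 evaluable and 100 to 105 enrolled by the usual unpooled and pooled formulas, not 90. If the full 20% is lost for the primary outcome, power is about 73% (72.7% exact, 73.5% pooled), 76.5% by the most favourable approximation, and 63.6% under Fisher's exact test. The risk of missing a true fall from 60% to 30% is then about 27%, or 36% with Fisher, against a stated 20%. These figures rest on the plan's own event rates, equal arms and loss spread evenly across them. If loss for the 48-hour outcome is really below roughly 7 to 11%, the 80% claim is met by chi-square, but the plan does not say that.

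**What to change.** Correct the Sample size calculation so that the number, the loss and the power agree. Suggested wording: *Ninety patients will be enrolled. With 20% loss, 72 will be evaluable, giving power of about 73% for 60% versus 30% with the uncorrected chi-square test at a two-sided 0.05 level. Power of 80% requires that no more than about 9% of patients lack the 48-hour outcome (exact enumeration; 7% by the pooled formula).*

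If the 20% was intended for the 3-month follow-up, say so, and give and justify a separate loss rate for the 48-hour outcome, with the power that follows from it.

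Name the uncorrected chi-square test as the primary test, and state the condition, if any, under which Fisher's exact test would replace it. That keeps the stated power tied to the test that will be run.

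The cost is a change of wording and a less favourable stated power. No extra patients are needed. Only if the sponsor wishes to keep both 80% power and 20% loss would enrolment have to rise, to 105 by the pooled formula (106 with equal arms).

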### Interim analyses

Because of the low-risk interventions, the short-term duration, and the small sample size, there are no interim analyses planned.

### Oversight and monitoring

#### Composition of the coordinating center and trial steering committee

This is a single-site study designed, performed, and coordinated at Beijing Tiantan Hospital. There is no steering committee or adjudication committee. Day-to-day running and management of the trial are based on the regular meeting and led by the chief investigator (CI, [name]). The study team meets via a teleconference or face-to-face at least twice a month. The content of regular meetings includes the following: (1) study investigators report the process of the trial, including recruitment, informed consent, assessment, and intervention procedures according to protocol; (2) trial managers raise the problems during the performance of the study; and (3) principal investigators provide oversight for all aspects of the trial and give support to study investigators in each link.

#### Composition of the data monitoring committee, its role, and reporting structure

In agreement with the Institutional Review Board (IRB) of Beijing Tiantan Hospital, a DSMB was not appointed for this study. Because this study is a short-term study, the interventional drugs of this trial are conventional clinical analgesics with safe dosages. The risks of the interventions are minimal. Moreover, enrolled subjects in this study are adjunctive to routine treatment through the spinal neurosurgery department in Beijing Tiantan Hospital. The population in this trial will be monitored carefully during hospitalization, and regular perioperative treatment will not be altered by study participation. Two knowledgeable anesthesiologists and a spinal neurosurgeon were responsible for the safety of this study. Once adverse events are suspected, they will be asked to diagnose whether the suspected adverse event is related to interventions and will guide the next treatments for safety measures when indicated. The study team will submit the annual tracking reports to IRB institutions to upload the process information of the study once a year. If there is any modification in this trial, the trial manager will need to submit the application in a timely manner, and the IRB will approve if it is feasible.

#### Adverse event reporting and harms

The follow-up investigators will pay close attention to the subjects during the intervention. If any adverse events (AEs) occur, the responsible investigator will report to the principal researcher immediately. If AEs are common and the patients’ symptoms are mild, we will supply thorough symptomatic support and treatments with close monitoring. If AEs become severe, the intervention will be stopped at once, professional doctors from various fields to immediately help the patients. Based on the relationships between AEs or serious adverse events (SAEs) and the drugs being assessed in this study, the project management team will consider whether unblinded allocated interventions are needed. If the AEs are so serious that they might impact regular clinical treatment and threaten patient safety, the research team will perform the emergency unblinding process and report the interventions to the surgeon in charge of the subjects at once. All AEs will be followed up until resolution. All adverse events will be documented in the final written report of this study and will be reported to the Institutional Review Board by the principal investigator.

### Patient and public involvement

Patients and the public were not involved in the trial design. Participants will have access to the findings of the study on request.

## Discussion

This proposed study will measure the efficacy and safety of esketamine combined with pregabalin on postsurgical pain in patients undergoing elective resection of spinal neoplasms. The participants will receive esketamine from the beginning of surgery until 48 h postoperation, along with a total dose of 150 mg pregabalin for 1 week postoperatively (POD 1~7, including the operation day) followed by a reduced dose of 75 mg pregabalin for the next week (POD 8~14). Both acute and chronic postoperative pain will be assessed during the 3 months after surgery. Other complications and safety outcomes will also be observed.

The primary concern is the potential inadequate analgesia in the control group after the surgery. The PCIA device is not a regular part of the therapeutic regimen during the postoperative period in this study hospital. As a result, we designed a usual PCIA procedure for all the participants to ensure basic postoperative analgesic treatment. If the participants experienced a moderate or severe level of pain, rescue analgesia was administered. The secondary concern is in regard to active placebo for the preoperative pregabalin capsule. In 2017, Hah’s team designed a randomized clinical trial to evaluate the effects of perioperative gabapentin on pain resolution in a mixed surgical population [17]. The researchers considered the sedating effects of preoperative gabapentin, so they chose lorazepam as the preoperative active placebo. Sleepiness is one of the common side effects of this kind of drug. However, in our pilot study, we did not observe obvious sleepiness in the participants before the surgery after taking pregabalin, and we will administer an injection of midazolam as a standard step after the patients enter the operating room; therefore, our research team decided to use the starch capsule as the placebo capsule at all time points. Furthermore, we chose total intravenous anesthesia as the standard maintenance of anesthesia with propofol and sufentanil, and propofol injection depended on target-controlled infusion (TCI). Our anesthesia management protocols might be different from those of previous studies. However, total intravenous anesthesia dependent on TCI technology can be more convenient to calculate and analyze possible drug interactions after the completion of the study. Moreover, we did not previously find any adverse events during the pilot study that are of concern, such as intraoperative awareness or delayed recovery.

The choice of the dosages of these two trial drugs was deliberate. Based on a related meta-analysis [3], intravenous ketamine does not increase complications related to the central nervous system (such as delirium and hallucinations). A meta-analysis [18] on the effect of pregabalin on chronic pain suggested that doses as high as 300~600 mg pregabalin per day do not increase the incidence of severe adverse events. Moreover, the guidelines on pain management [10] have suggested the following recommended dosages of these two drugs: a 0.5-mg/kg bolus of ketamine with a continuous intravenous infusion dose of 0.12 mg/kg h (2 μg/kg min) and a maximum continuous infusion dose that does not go over 10 μg/kg min; a 150~300-mg preoperative dose of pregabalin and a postoperative dose of 150~300 mg per day. Based on the above information, these two trial drugs in our study will be used at lower dosages. The purpose of this dose design is to keep the participants as safe as possible while relieving postsurgical pain.

In conclusion, this study is a randomized controlled trial to explore a better method to treat postsurgical pain. The expected outcome is that perioperative esketamine combined with pregabalin can safely and effectively relieve postsurgical pain, and the results of this study can expand the understanding of perioperative pain management.

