The mechanisms underlying postsurgical pain might be peripheral and central sensitization because of nerve injury and inflammatory responses at the operative site. Previously, researchers have suggested that central pain sensitization might be related to N-methyl-d-aspartate (NMDA) receptor activation [11]. Ketamine, an NMDA receptor antagonist, reduces central pain sensitization by blocking the activity of NMDA receptors. A related meta-analysis found that intravenous ketamine could reduce VAS scores in the 24~48-h postoperative period and decrease opioid consumption [12]. S-Ketamine, one of the enantiomers of ketamine, is a more effective analgesic and has fewer side effects than ketamine. Regarding the effects of S-ketamine on acute postsurgical pain, a meta-analysis of 12 randomized controlled trials showed that intravenous S-ketamine could decrease the intensity of pain and opioid requirements only 24 h after surgery and may increase the incidence of psychotomimetic adverse events [13]. Unfortunately, the evidence level was only moderate or even low. Due to the differences in the S-ketamine intervention protocols and the types of surgery, more high-quality studies are needed.

At the same time, gabapentinoids (gabapentin and pregabalin) have gained more attention from researchers for their significant effect on neuralgia. These compounds can inhibit the modulation of neuronal excitability by blocking α2–δ subunits of presynaptic, voltage-dependent calcium channels, which are upregulated in central sensitization processes [11]. A meta-analysis of preoperative gabapentinoids for acute postoperative pain reported that gabapentinoids were associated with reduced pain scores and cumulative morphine consumption during the 48-h postoperative period [1]. In the same year, another meta-analysis showed the effectiveness of preoperative pregabalin on acute postsurgical pain [14]. In contrast, in 2020, a meta-analysis including 281 trials investigated the effect of perioperative gabapentinoids on postoperative acute pain and reported the noneffective analgesic effects of gabapentinoids in adult patients during the postoperative period [15].

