### Intervention

In the combined group, the patients will be given both esketamine and pregabalin during the perioperative period. The patients will receive 2 capsules of pregabalin (75 mg/capsule, 150 mg total) 1~2 h before the surgery and 1 capsule twice daily during the 7-day postoperative period (75 mg/capsule, BID; 150 mg total; POD 1~7), followed by dose reduction to 1 capsule once daily for 7 days (75 mg/capsule, QD; 75 mg total; POD 8~14). At the same time, patients will be administered a bolus dose of 0.5 mg/kg esketamine after the induction of anesthesia and then receive continuous intravenous infusion at 0.12 mg/kg ·h (2 μg/kg ·min) during the 48-h postoperative period.

In the control group, the patients will be given the same number of placebo capsules as the combined group at the same time points (two placebo capsules 1~2 h preoperatively and twice daily postoperatively for 7 days, followed by a reduction to a single capsule once daily for 7 days), alongside a normal saline bolus after induction of anesthesia and intravenous saline infusion for the 48-h postoperative period.

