### Provisions for posttrial care

All of the participants will receive conventional postoperative care in the ward. The postoperative treatment will not be changed whether the patients enter the trial. The interventions of this trial are a combination of analgesic management added to the basic analgesic treatment, which will help the patients to get more comfortable feelings. The interventions are common drugs in the clinic, and the dosages are lower. Thus, the patients will be at low risk during the interventional period. Therefore, there is no anticipated harm or special posttrial care for the participants.

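### The listed adverse-event checks end at POD3 while study capsules continue to POD14, and the dose wording used to argue low risk does not match the plan's own figures

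*Protocol article*

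**What the plan says.** **Dosing (Intervention).** Capsules: two before surgery (150 mg pregabalin or placebo), one twice daily on POD1–7, one daily on POD8–14. Infusion: "a bolus dose of 0.5 mg/kg esketamine after the induction of anesthesia", then 0.12 mg/kg/h until 48 h after surgery.

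**Safety assessment (Outcomes).** Psychotic effects are rated with BPRS and CADSS at 2 h, POD1, POD2 and POD3. The adverse-event item names palpitation, hypertension, dizziness and diplopia as drug-related, adds complications, PONV and delirium, and closes with the same four times. Other instruments are already scheduled at discharge (QoR-15, PHQ-9, GAD-7) and at 1 and 3 months; post-discharge outcomes are collected by telephone.

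**General surveillance (Adverse event reporting and harms).** Investigators watch participants closely while treatment lasts, report events to the principal researcher at once and follow them until they resolve. No contact times are given.

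**Dose rationale (Discussion).** The guideline regimen is given as "a 0.5-mg/kg bolus of ketamine with a continuous intravenous infusion dose of 0.12 mg/kg h", with an infusion maximum of 10 µg/kg/min, and pregabalin 150–300 mg before surgery and 150–300 mg per day after it. The conclusion drawn is "Based on the above information, these two trial drugs in our study will be used at lower dosages".

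**Use of that rationale (Provisions for posttrial care).** "The interventions are common drugs in the clinic, and the dosages are lower"; low risk during treatment is inferred directly from this.

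**Routine care.** The section on the data monitoring committee says participation does not change usual perioperative treatment. The Discussion says PCIA is not standard at this hospital and was set up for all participants.

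**The concern.** The trial undertakes to examine the safety of a two-drug regimen, one part of which is taken for two weeks. If systematic questioning stops at POD3, later events enter the data only when a participant volunteers them or staff happen to notice them. Such capture is incomplete. Suppose a fraction c of late events is recorded equally in both arms: the observed risk difference is then c times the true one, so a real excess of dizziness or diplopia looks smaller than it is. Blinding helps keep c similar between arms but does not bring it up to 1.

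The wording problem is of a different kind. A reader who relies on the article's statement that doses are reduced would judge the regimen milder than the quoted guideline figures show. The statement about unchanged routine care has the same weakness, since the PCIA was introduced for the trial.

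**Working it through.** **1. Esketamine against the quoted ketamine figures** (Intervention; Discussion).
- Unit check: 0.12 mg/kg/h × 1000 / 60 = 2.0 µg/kg/min. The plan's own conversion reproduces.
- Bolus: 0.5 / 0.5 = 1.00.
- Infusion: 0.12 / 0.12 = 1.00. Against the stated maximum: 2 / 10 = 0.20.

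**2. Pregabalin against the quoted range.**

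| Period | Trial dose | Ratio to lower limit (150 mg) | Ratio to upper limit (300 mg) |
|---|---|---|---|
| Preoperative | 150 mg | 1.00 | 0.50 |
| POD1–7 | 2 × 75 = 150 mg/day | 1.00 | 0.50 |
| POD8–14 | 75 mg/day | 0.50 | 0.25 |

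Only the last row lies below the range.

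**3. Capsule exposure after the last listed adverse-event time (POD3).**
- Days: 14 − 3 = 11; 11 / 14 = 79%.
- Postoperative capsules: 7 × 2 + 7 × 1 = 21 in total; POD1–3 account for 3 × 2 = 6; 21 − 6 = 15; 15 / 21 = 71%.
- Counting the two preoperative capsules: 15 / 23 = 65%.
- Pregabalin in the combined group: total 150 + 7 × 150 + 7 × 75 = 1725 mg; after POD3, 4 × 150 + 7 × 75 = 1125 mg; 1125 / 1725 = 65%.

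**4. Sensitivity to day numbering.** The counts in step 3 use one numbering for dosing and assessment. The Discussion counts the operation day within POD1–7; the Intervention section describes seven postoperative days. If dosing day 1 were the operation day but the assessments counted from the day after, POD3 would be dosing day 4. That leaves 14 − 4 = 10 of 14 days, and 3 × 2 + 7 = 13 of 21 capsules (62%). The conclusion does not change.

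**5. Which events the gap concerns.** The infusion ends at 48 h, so the four rating times for psychotic effects span it. The gap is confined to the capsules.

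**6. Grammar of the adverse-event item.** The four times close a list and could be read as belonging to delirium alone. Drug-related events would then have no listed time at all, so reading the times as applying to the whole item is the more favourable reading.

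**The case against.** **On the schedule.** Recording of adverse events does not stop at POD3. The harms section covers the whole intervention, requires immediate internal reporting and follows every event to resolution. The schedule figure is not shown, and the article condenses a fuller protocol, so a later check may exist. This stands as a limit on certainty. It does not remove the point: the text does list times, they end at POD3, and unscheduled watchfulness is not the same questions put to everyone at the same time.

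**On the dose wording.** Read loosely, as towards the low end of everything cited, the sentence can be defended: the infusion is a fifth of the stated maximum, and pregabalin is well under the 300–600 mg per day of a cited meta-analysis. But the maximum is a ceiling, and the bolus has no higher comparator in that paragraph. A reader might also argue that an equal mg/kg dose of esketamine is in effect a higher one. The Background says S-ketamine "is a more effective analgesic and has fewer side effects than ketamine", which cuts both ways for a safety argument, so the point should rest on the equal figures alone.

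**Stronger readings that the document does not support.**
- A reader might infer that the dose claim is why there is no DSMB or interim look. The interim statement is "Because of the low-risk interventions, the short-term duration, and the small sample size, there are no interim analyses planned", and the DSMB text cites safe dosages, conventional drugs, short duration and agreement with the ethics board. Neither calls the doses lower, and nothing ties the POD3 end point to dose.
- A reader might infer that no outside body sees safety data before enrolment ends, from "The study team will submit the annual tracking reports to IRB institutions". The reporting date is not stated, and the principal investigator also reports adverse events to the board.
- A reader might infer that the ethics board and patients were given a wrong rationale. Neither the submission nor the consent form is available here.
- The psychotomimetic signal in the Background ("may increase the incidence of psychotomimetic adverse events") is not ignored: BPRS and CADSS are scheduled for it, and the expectation of no harm is stated in the context of post-trial care.
- The two day-numbering descriptions concern capsule dosing; nothing shows that the assessments are shifted by 24 h.

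**Conclusion.** The point holds in a limited form. On the text available, 11 of 14 postoperative dosing days and 15 of 21 postoperative capsules (71%) fall after the last listed adverse-event check, so the between-group comparison of late drug-related events rests on unscheduled reporting. This assumes that the missing figure adds no later check and that dosing and assessment days are numbered alike; a mismatch of one day would still leave 10 of 14 days.

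The dose finding needs no assumption. Esketamine is given at the same mg/kg figures as those quoted for ketamine. Pregabalin is at the bottom of the quoted range through POD7 and below it only on POD8–14. Calling the doses lower is wrong for esketamine against the recommended regimen and loose for pregabalin, so it should not carry the inference of low risk. Correcting it changes the reasoning on paper, not what is done to patients. The statement that routine care is unaltered also conflicts with the PCIA set up for participants.

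None of this shows that the regimen is unsafe, that the doses should change, or that the decision against a DSMB was wrong.

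**What to change.** 1. Ask the drug-related adverse-event questions (at least the named symptoms such as dizziness and diplopia) also at discharge and at the 1-month telephone call already scheduled. Word the 1-month question to cover the period to POD14, and include these events in the safety comparison between groups. If the full schedule already has such a check, state it in the text.
2. In the Discussion and under Provisions for posttrial care, replace the dose statement: esketamine at the mg/kg figures quoted for ketamine; pregabalin at the lower end of the quoted range through POD7 and below it on POD8–14. Base any low-risk statement on something other than reduced dose.
3. Reconcile the claim of unaltered perioperative treatment with the introduction of PCIA for all participants.

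The cost is a few extra questions at existing contacts, with slightly longer interviews, and a protocol modification submitted to the ethics board. Recall at 1 month of events in the first two weeks will be imperfect, but the same questions go to both blinded arms. No change of dose is proposed.
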